### Health economic analysis plan

Economic analysis will be undertaken to investigate short term and longer term potential cost-effectiveness of NRT in pregnancy. The cost-effectiveness of NRT use by the general population has been established [33] and a small number of studies have investigated the potential cost saving of smoking cessation interventions in pregnancy. [34], but few have used empirical data on costs of interventions. Analyses for this study will be primarily undertaken from an NHS perspective. Uptake of behavioural support and NRT will be monitored and costs of both estimated with both locally-specific and national average values. The differential consequences in terms of length of maternal stay and post natal delivery to special care between the two arms of the trial will be used with the estimated costs of delivering interventions with and without NRT patches and differential smoking cessation rates to estimate the incremental cost-effectiveness ratio. Sensitivity analyses exploring assumptions made in estimating the control state (no NRT) will be undertaken. The primary health outcome will be maternal smoking cessation immediately before delivery and differences in health status at 6 months (from EQ5D data) will be converted into QALYs to allow cost-utility modelling. Additionally, a range of modelling techniques will be used to estimate longer-term cost-utility from two year follow-up data. Epidemiological and economic models will be used to estimate lifetime gains in QALYs from smoking cessation and savings in health care expenditures [33,35]. A full literature review will be undertaken to explore the potential for providing monetary estimates of the long term impacts on the child of their differential birth outcomes.

### Safety

To minimise the likelihood of women or infants being harmed by unexpected effect(s) of nicotine that could not predicted from previous research, the Data Monitoring & Ethics Committee will have access to birth outcome data. These data will be available for the DMEC to analyse as is considered appropriate to investigate whether or not significant or clinically-important differences arise between study groups (e.g. in birth weight).

### Safety reporting

The following will be considered ***adverse events *(AEs)**:

Withdrawal from patch treatment due to i) skin reaction or ii) other symptom(s) which are potentially caused by NRT (listed in section 4.10 BNF)

AEs will be reported in an annual safety report to the MHRA, REC and Sponsor.

The following will be considered ***Suspected Unexpected Severe Adverse Reactions ***(SUSARs):

*Baby*: fetal death, still birth, neonatal and post-neonatal death, congenital abnormality, special care admission (excluding transitional care admission)*

*Maternal*: eclampsia, maternal death, some hospital admissions* (see below)

*Birth outcome*: placental abruption, premature birth (earlier than 32 weeks)*, low birth weight (< 2,500 g)

The following hospital admissions are **not** SUSARS: admission for delivery, uncomplicated false labour, unconfirmed fetal compromise (i.e. baby well), vaginal bleeding of no serious cause and infant hospital admissions ***after*** the neonatal period

Any other serious unexpected event.

All SUSARs except those marked with an asterisk* are considered life threatening.

Life threatening or fatal SUSARs (no asterisk) will be reported to the MHRA and REC within 7 days (follow up report within 15 days) and also to relevant NHS trust R&D office according to local policies.

Non life threatening SUSARs (asterisk) will be reported to the MHRA and REC within 15 days and also to R&D offices, as appropriate.

SUSARs will also be reported to the DMEC chair along with the treatment allocation group of the trial subject and a cumulative count of SAE and SUSAR frequency in each trial arm.

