### Follow-up at one month after agreed quit date

Participants will return to the research midwife (RM) for further supplies of patches. To allow some flexibility this follow up will occur between 3 and 6 weeks after randomisation. The RM will ascertain women's smoking status and those who report not smoking regularly (confirmed by exhaled CO measurement) will be issued with a new trial treatment pack number (obtained by the RM from the online database) and will receive a corresponding treatment pack (containing 4 weeks' patches). A saliva sample to measure cotinine levels on treatment will be taken. The Trial Office will send a postal questionnaire asking about smoking status to women who do not return at one month. One postal and telephone reminder will be used. When women report continued smoking cessation and do not attend for further NRT, the research midwife will contact them to arrange CO validation of this, visiting them at home, if necessary.

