### Data monitoring by RM between data collection points

These data are required to ensure that the Data Monitoring and Ethics Committee is provided with adequate information to form an opinion concerning trial safety:

Development of major fetal abnormality between randomisation and labour onset

Fetal death between randomisation and labour onset

Maternal death between randomisation and labour onset

Hospital admission

Each month the Trial Office will provide RMs in the 5 centres with a list of trial numbers for participants who are still pregnant. The RM will use these to access subjects' computer records to obtain the information listed above. In the event of a hospital admission the RM will assess whether or not a serious adverse event has occurred and act accordingly see below. If the RM enters a fetal death into the database, this will automatically prevent further infant follow up and the RM will liase with the mothers' obstetrician to determine whether or not asking for follow up information concerning smoking behaviour around the anticipated time of delivery is acceptable. Major fetal abnormalities will also be reported to the trial office who will review these individually before deciding whether or not the participant should be allowed to continue within the trial.

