### Data collection

Here the specific items of data to be collected at different points during the trial are outlined.

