#### b) One month after quit date

RM collects data from those who return. Postal questionnaires sent from NTCT to those who do not. The following data are collected:

RM notes *whether or not follow up occurs *and the *date of any follow up*. RM also inspects participants' supply of patches to calculate the number used.

Smoked at all in the previous 24 hrs

*Smoked since quit date *(further details on outcomes form 1)

Exhaled CO reading

On how many days have patches been used?

On how many days (if any) have non-trial patches been used?

How many behavioural support sessions with NHS stop smoking services used (telephone & face to face)?

Saliva sample for cotinine estimation taken

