#### c) Upon admission for childbirth

The following data are recorded by the RM or delivery suite staff:

Date of follow up/exhaled CO reading or saliva sample

Smoked at all in the 24 hrs prior to delivery

Smoked between quit date and delivery

One or both of, *i) exhaled CO reading & ascertainment date ii) saliva sample *(for cotinine)

On how many days have patches been used?

On how many days (if any) have non-trial patches been used?

How many behavioural support sessions with NHS stop smoking services used (telephone & face to face)?

i) These data obtained by RM from ***maternal ***or ***infant medical records before ***discharge. For reasons of data protection some personal infant details are recorded on paper rather than being transmitted over the internet to the trial database:

*maternal *

hypertension (>140/90) on 2 occasions (excluding labour)

miscarriage (between randomisation and 24 weeks)

labour onset (spontaneous, induced, no labour)

mode of delivery (SVD, instrumental, caesarean)

ante natal or post natal maternal hospital admission

*infant*

baby initials

D.O.B

Gender

Baby NHS number

*Prompt for RM to confirm full name and address and contact details of baby and to record these on paper *(see below)

Prompt for RM to make a new record of contact details if these have differed from previous (i.e. maternal) ones

baby hospital number

birth weight

Number of births

if multiple birth, indicate number and birth order

live or stillbirth?

cord ph < 7.0

Apgar <7 at 5 min

*Gestational age at birth *– to be calculated within database from gestation at recruitment

These infant personal details will be recorded on paper only:

baby name

baby address (inc postcode)

ii) These data obtained by research midwife from ***infant medical records after ***discharge:

If live birth? live on leaving hospital

ventilation > 24 hrs

necrotising enterocolitis

neonatal convulsions

admitted to special care

*intraventricular haemorrhage *(4 categories)

*congenital abnormality present (y/n). If y then free text to describe this*.

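### A non-serious patch reaction counts as an adverse event only if the woman stops patches because of it, and no listed data item records symptoms or the reason for stopping

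*Protocol article*

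**What the plan says.** The Safety reporting section of the protocol article defines adverse events by a list with a single entry: "Withdrawal from patch treatment due to i) skin reaction or ii) other symptom(s) which are potentially caused by NRT". It then says "AEs will be reported in an annual safety report to the MHRA, REC and Sponsor". A second, longer list in the same section covers serious fetal, infant, maternal and birth events. It ends with "Any other serious unexpected event" and does not depend on stopping patches.

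The Data collection section introduces its lists with "Here the specific items of data to be collected at different points during the trial are outlined". At one month the items on patches are a count of the supply by the research midwife, "On how many days have patches been used", and days of non-trial patch use. On admission for childbirth they are again days of patch use and "On how many days (if any) have non-trial patches been used". For women who miss the one-month visit, the Trial Office "will send a postal questionnaire asking about smoking status to women who do not return at one month".

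The section on withdrawal from patch treatment requires follow-up to continue whatever the reason for stopping. It does not ask for the reason to be recorded.

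**The concern.** The definition makes the woman's decision to stop part of the event. Two kinds of reaction can then go uncounted:

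- **Tolerated reactions.** If the woman keeps using patches, her reaction is excluded by definition.
- **Reactions that led to stopping.** These qualify only if someone learns the reason, and no listed item asks for it. Days of use cannot separate stopping for a rash from stopping after relapse or by choice.

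The one-month visit is described as a return for more patches. A woman who stopped because of a reaction has less reason to attend, although the documents do not show how often this would happen.

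The trial is meant to establish whether standard-dose patches are safe as well as effective in pregnancy. A low adverse event count sent each year to the regulator, the ethics committee and the sponsor could be read as good tolerability when it partly reflects what was never asked.

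**Working it through.** The protocol states no patch-reaction rate and no capture rate, so there is no plan figure to reproduce. The finding rests on setting the sections side by side. The arithmetic only illustrates what under-capture does.

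**Step 1. Can the definition be applied from the listed items?** It needs two facts: that a symptom occurred, and that it was why patches were stopped.

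| Contact or section | What is listed that bears on patches or reactions | Symptom item | Reason for stopping |
|---|---|---|---|
| One-month visit | Patch count, days of use, days of non-trial use | None | None |
| One-month postal questionnaire | Smoking status. If the Data collection list also governs it, days of use as well | None | None |
| Childbirth | Days of use, days of non-trial use | None | None |
| Monthly record check by the midwife | Fetal abnormality, fetal death, maternal death, hospital admission | Only if it leads to admission | None |
| Withdrawal from patch treatment | Follow-up continues | None | None |

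Neither fact is among the listed items, so qualifying withdrawals come to light only if volunteered.

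**Step 2. Equal under-capture in both arms.** Input from the Sample size section: 525 women per arm. All reaction rates and capture fractions below are assumptions.

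Expected count = 525 × true rate × capture fraction.
z = (p1 − p2) / √(2 × p̄ × (1 − p̄) / 525), where p̄ is the mean of the two captured proportions.

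Assume true rates of 10% on NRT and 4% on placebo. Suppose one third of affected women stop, and the reason is learned for half of those, so 1/3 × 1/2 = 1/6 are captured.

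- All captured: 52.5 v 21, ratio 2.5. p̄ = 0.070, z = 0.06 / 0.01575 = 3.8.
- One third captured: 17.5 v 7, ratio 2.5. p̄ = 0.0233, z = 0.02 / 0.00932 = 2.1.
- One sixth captured: 8.75 v 3.5, ratio 2.5. p̄ = 0.0117, z = 0.01 / 0.00663 = 1.5 (about 1.4 if rounded to 9 v 4).

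Now assume true rates of 20% on NRT and 10% on placebo, with a two-sided 5% test:

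| Captured in both arms | Expected events, NRT v placebo | Risk difference | Risk ratio | Power |
|---|---|---|---|---|
| 100% | 105 v 52.5 | 10 points | 2.0 | 99.5% |
| 50% | 52.5 v 26.2 | 5 points | 2.0 | 87% |
| 25% | 26.2 v 13.1 | 2.5 points | 2.0 | 57% |
| 10% | 10.5 v 5.2 | 1 point | 2.0 | 26% |

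The absolute difference and the power fall. The ratio does not move.

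**Step 3. Unequal capture.** With the same 20% v 10%, observed ratio = (0.20 × NRT capture) / (0.10 × placebo capture):

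- 30% v 20% captured: 0.06 / 0.02 = 3.0
- 20% v 30% captured: 0.04 / 0.03 = 1.33
- 20% v 40% captured: 0.04 / 0.04 = 1.0

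A true ratio of 2 can be inflated or erased, depending on which arm loses more.

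**The case against.** The strongest reply has four parts.

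**This is a journal article.** It outlines the data items and refers to an outcomes form that is not shown. The full protocol may hold an adverse event or withdrawal form, and a definition that turns on the reason for withdrawal suggests someone meant to record it. This stands in part. A reader might infer that no form asks why patches were stopped, but the article shows only that no listed item does. The definition itself is stated outright, and an unseen form would not bring tolerated reactions within it.

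**Serious harm does not depend on this definition.** This stands in full. The serious-event list is independent of patch withdrawal. For admissions, "In the event of a hospital admission the RM will assess whether or not a serious adverse event has occurred", and the chair of the data monitoring committee receives cumulative serious-event counts by arm. Birth outcomes come from medical records. The gap concerns non-serious reactions only, so it would be wrong to infer that all adverse events in the trial depend on withdrawal.

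**No tolerability comparison is planned.** This also stands. Patch reactions are not among the outcome measures, and the analysis plan compares fetal and maternal birth outcomes. A reader might infer that a planned between-arm comparison is biased towards no difference. The documents do not support that. There is no such comparison, women and midwives are blind to allocation, equal under-capture leaves the ratio unchanged, and unequal capture can act either way. Exposure after week four may also differ by arm, because the second patch supply goes only to women who are not smoking, which makes the direction less certain still.

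**Counting only reactions that cause withdrawal is a legitimate choice.** It contradicts nothing else in the article, and women with known patch sensitivity or chronic generalized skin disorders are excluded. Even so, a rule that discards tolerated reactions is a poor fit for a trial with a stated safety aim, and the rule as written still needs the reason for withdrawal.

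**Conclusion.** The point holds for non-serious events and should be acted on. As written, the definition leaves out reactions in women who keep using patches, and the listed items give no means of identifying those who stop because of a reaction. Non-serious patch reactions will be under-ascertained in the annual safety report and in anything the trial later says about tolerability.

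The size cannot be given, because the documents contain no reaction rate, no stopping rate and no capture rate. A claim that reactions will be badly undercounted would have no figure behind it. The illustrations show loss of information under equal capture, not a bias of known direction. No effect on the planned analyses of cessation or birth outcomes is shown.

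The conclusion assumes that the listed items are a fair account of what is asked about patches at each contact. If an unseen form records reasons for stopping, the second half of the point falls away and the narrow definition remains.

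**What to change.** 1. In Safety reporting, define a non-serious adverse event as any skin reaction or listed NRT-type symptom during patch use, whether or not patches are stopped. Leave the serious-event list as it is.
2. Add two items to the one-month contact (visit, postal questionnaire and telephone reminder) and to the childbirth contact: skin reaction or other symptom while using patches (yes/no, type), and patches stopped early (yes/no, date, reason).
3. Tabulate both items by arm. Withdrawals because of a reaction remain available as a subset.
4. If the full protocol already has a form that records the reason for stopping, name it in Safety reporting and add only the symptom item.

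The cost is one changed definition and two short items on contacts that already take place. Forms become slightly longer and there are more non-serious events to tabulate. No treatment rule changes.

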## Discussion

Recruitment to the SNAP trial will start in 2007 and at the conclusion of the trial, it should produce valuable information about the safety and efficacy of NRT use in pregnancy.
